#### Session content

In Session 1, the theme is, “Any emotion is a dear friend.” Participants will learn about resilience and its protective factors. The relationship between parental resilience and its impact on children will be explained. ER will be introduced as one of the protective factors. Participants will learn the meaning and importance of negative emotions, including anger, and why and how they occur. Eight ER skills will be taught in a realistic, applicable way. Using CR skills, participants will learn to recognize the underlying irrational cognitions and unrealistic expectations that may cause negative emotions. The homework assignment is to keep an anger log to monitor anger, to use an anger scale to express anger appropriately to their family, and to encourage their children to do the same.

In Session 2, the theme is, “Worry less and trust more.” Participants will learn how to apply the emotion regulation skills they learned in Session 1 to improve their relationship with their children. The development of children’s brains and emotions will be explained, including the important role of tantrums in the developmental process. In this session, participants will also learn how harsh verbal discipline negatively affects children’s brains and how to avoid it. They will learn how to reframe children’s weaknesses as strengths. The homework assignment is to conduct active listening and to find and verbally appreciate ordinary but appropriate behavior of their children instead of paying attention to and criticizing their misbehaviors and record them. Another assignment is to show empathy and validate children’s feelings when they throw a tantrum without changing the standard or rule.

In Session 3, the theme is, “Difference is strength.” Participants will learn how to improve their relationship with their partners applying the ER skills they learned in the first two sessions. They will discuss how men and women differ in many aspects. They will learn to use CR to recognize their partners’ weaknesses, or the differences between them, as strengths and be introduced to problem-solving strategies. They will be asked to write down five good characteristics of their partners and five things they are grateful for in relation to their partners. The homework assignment will be to tell their partners what they wrote down and to ask them to do some simple tasks, specifically expressing gratitude and appreciation.

In Session 4, the theme is, “I love and trust myself no matter what.” Participants will learn that self-esteem and anger are related, and that self-compassion and self-acceptance are the best skills they could develop – not only for themselves but also for their children’s happiness and resilience. Next, a small number of exercises will be conducted in pairs: drawing a lifeline, looking back at the past, sharing the strengths they have gained at their lowest moments, writing a “thank me letter,” and reading the letters to each other. They will discuss and share what they have learned and achieved through the program and the small, simple things they will continue to do for themselves and their families. The homework assignment is to use positive self-affirmation more often and give themselves a break to enjoy themselves.

#### Control group

Participants in the control group will attend discussion meetings led by a discussion leader, where they will be able to discuss their problems and share how they cope with them. No judgment or criticism will be given. After the two-month follow-up questionnaire, the control group will have the opportunity to participate in the same intervention. Partners will not participate in the discussion meetings.

### Babysitting support

A babysitting service, housed in a different room in the same building, will be available to participants of both groups upon request.

### Outcomes

#### Primary outcome

##### Resilience

Psychological resilience will be measured using the Psychological Resilience Scale [42], which consists of three subscales and a total of 21 items. Items are scored on a five-point Likert scale. Examples of items are “I’m curious about many things” (novelty pursuit); “I can control my anger” (ER); and “I believe I have a bright future” (positive future outlook). Higher scores indicate a higher degree of resilience.

#### Secondary outcomes

##### State-trait anger expression inventory

This widely used scale is a 44-item measure designed “to provide a means of measuring various components of anger” [43]. It includes the following subscales: state anger (how you feel now), trait anger (how you usually feel), anger-in (how you suppress anger), anger-out (how you express anger, aggression or insults to others), and anger control (how you control anger or do not express it or express it more appropriately). Since anger is felt differently when directed toward different people, we will assess anger toward both children and partners in terms of how it is expressed —i.e. anger-in, anger-out, and anger control.

##### Self-esteem

Self-esteem will be measured by the Japanese version of Rosenberg’s Self-esteem Scale [44]. This is a 10-item inventory with higher scores indicating a higher degree of self-esteem.

##### Parental attitude

The parenting attitude scale consists of five subscales measuring four negative and one positive attitude [45]. Examples of items are: “I can’t do what I want to do, I’m spending too much time on parenting” (burden of parenting), “I feel disgusted when children keep making a mess” (burden from children’s attitude and behavior), “I’m not confident about my parenting” (anxiety about parenting), “I’m afraid my child is more childish than other children” (anxiety about child’s development), and “I feel I’m growing through parenting.” (positive attitude toward parenting). Higher scores indicate a higher degree of each attitude.

##### Problem-focused coping strategies

The Problem-Focused Coping Strategies Scale [46] will be used to measure how caregivers cope with stressful situations. The measure consists of five subscales: solution calculation, concrete solution behavior, gathering information, goal orientation, and seeking solutions. We will use the first two scales, which will be enhanced for the purposes of this program.

*Family functioning* will be measured by the Japanese version of Family APGAR [47]. This measure consists of five parameters of family functioning: adaptability, partnership, growth, affection, and resolve. Items will be scored on a four-point scale, with higher scores indicating a higher degree of family functioning.

##### Cognition of children’s behavior

The Attribution on Children’s Misbehavior Scale consists of three subscales and measures the cognition of the attitudes and behavior of children [48]. Examples of items are: “I feel judged as ‘a bad parent’” (hostile attribution), “I struggle not knowing how to handle my child” (negative attribution), and “It’s a natural part of growing up” (positive attribution).

### Data collection

The outcome measures will be assessed online at the baseline, post-intervention, and at a two-month follow-up. Demographic data will be collected at the baseline and a program evaluation survey will be conducted post-intervention. Partners will be assessed (using the same measurement as for mothers) to evaluate the indirect impact from mothers sharing the knowledge and skills they gained in the sessions or discussions or seeing the changes in mothers’ attitude or behavior by participation.

### Statistical analysis

Data will be analyzed according to the intention-to-treat principle. The primary and secondary outcome measures will be analyzed at post-intervention and two-month follow-up using analysis of covariance to adjust for baseline differences between the groups. Subgroup analysis will be conducted using stratification factors including mother’s age, the area they live in, and number of children.

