**Methods:**

We designed a two-arm, parallel, randomized trial with an active control. Mothers and their partners with children between three and six years old will be recruited. Following an online baseline survey, 140 mothers will be randomly allocated to either an intervention or control group. Self-report assessment will be conducted online post-intervention and at a two-month follow-up. The control group will participate in a serious of group discussions. The intervention group will participate in four bi-weekly 120-min sessions of a Cognitive Behavior Therapy-based program designed to enhance resilience, focusing on emotion regulation through cognitive reappraisal. Participants will be encouraged to apply and share the skills they acquire with their partner and children at home. Partners will also be assessed to explore their indirect influence from the mothers. Intention-to-treat analysis will be conducted and the two groups will be compared, applying covariate analysis. The primary outcome of the intervention is improved resilience. Secondary outcomes include improved anger control, self-esteem, cognition of children’s misbehavior, and reduced parental stress.

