## Methods/design

This is a non-blinded study with two parallel arms and an active control group (see Fig. 1). The allocation ratio of both groups is 1 to 1.

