### Sample size calculation

Sample size was calculated using a statistical power analysis. To detect an effect size of d = 0.62 between the two conditions, with α = .05 (two-tailed) and β = 0.8, 64 dyads in each group are needed. Considering attrition possibility and feasibility, 140 mothers and their partners will be recruited.

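### The primary outcome is analysed at two time points of equal standing, none is named as primary, and no rule says whether one or both must be significant

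*Protocol article*

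**What the plan says.** - **Statistical analysis:** "The primary and secondary outcome measures will be analyzed at post-intervention and two-month follow-up using analysis of covariance". Neither time point is ranked above the other.
- **Abstract, Methods:** "The primary outcome of the intervention is improved resilience", with no time attached.
- **Primary outcome, Resilience:** the instrument is the Psychological Resilience Scale, "which consists of three subscales and a total of 21 items". No time point is given, and the total score is not expressly named as the endpoint.
- **Data collection:** lists baseline and the two later assessments without ranking them.
- **Sample size calculation:** one between-group effect ("To detect an effect size of d = 0.62 between the two conditions") at "α = .05 (two-tailed"), giving "64 dyads in each group are needed". It does not say at which assessment the effect is expected.
- **Discussion:** the hypothesis predicts better resilience than in the discussion group, again without a time.

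**The concern.** The sample size rests on one comparison, while the analysis section provides for two comparisons of the primary outcome. Nothing connects them: there is no primary time point, no order, no split of α and no requirement that both succeed.

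Two things are at stake. First, if either time point may carry the efficacy claim, the primary conclusion is not held at the planned 5%. Second, if one time point is significant and the other is not, the plan does not say what the trial has shown. The reading would then be chosen after the results are known, in a trial that is non-blinded with self-reported outcomes. Fixing the endpoint in advance is one of the few safeguards such a design has.

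**Working it through.** **Inputs.** From the article: two-sided α = 0.05, d = 0.62, 64 per group, 1:1 allocation, two analysis times. Assumed: the correlation ρ between the two test statistics, because the article gives none. With ANCOVA this is roughly the correlation between the two later scores after adjustment for baseline. I use 0.5 to 0.9 as the working range and zero as the limiting case.

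**Step 1: the plan's own figure.** Reading the stated 0.8 as power, n per group = 2(1.960 + 0.842)² / 0.62² = 2 × 7.85 / 0.3844 = 40.8, so 41 (42 with the t distribution). The stated 64 is not reproduced; it comes out with the t distribution at d = 0.50. That is a separate matter, and nothing below depends on it. What matters here is that the calculation is for a single test at 0.05.

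**Step 2: false-positive rate if either time point counts.** With no true effect at either time, the two statistics are approximately bivariate normal with correlation ρ:

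- Two-sided: 1 − P(|Z₁| < 1.96 and |Z₂| < 1.96).
- In favour of the intervention only: 1 − P(Z₁ < 1.96 and Z₂ < 1.96), against a nominal 2.5%.

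In the independent case these are 1 − 0.95² = 9.75% and 1 − 0.975² = 4.94%.

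| Assumed ρ | Two-sided | Favouring the intervention |
|---|---|---|
| 0 | 9.75% | 4.9% |
| 0.5 | 9.1% | 4.5% |
| 0.6 | 8.8% | 4.4% |
| 0.7 | 8.3% | 4.2% |
| 0.8 | 7.8% | 3.9% |
| 0.9 | 7.0% | 3.5% |
| 0.99 | 5.7% | 2.8% |

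The two-sided rate exceeds 5% for every ρ below 1.

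**Step 3: other success rules.** If both time points had to be significant, the rate could not exceed 5%, but power would be lower than for one test. If one time point is primary and the other is tested only after it succeeds, the rate is 5.0%: when the first null hypothesis is true, any false claim requires rejecting it, and when only the second is true, it is tested once at 0.05. The error rate therefore depends wholly on a rule that the article does not give.

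**Step 4: what an α split would cost.** At 0.025 per test, 80% power at d = 0.62 needs 51 per group, and 64 per group gives 89%. The two-sided rate is then 4.9% at ρ = 0 and 4.3% at ρ = 0.7.

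**The case against.** The strongest objection is one of scope. This is a journal article with a very short analysis section, and testing order and α allocation are often left to an analysis plan. That is fair for the mechanics of an adjustment, and their absence alone would be no finding. It does not cover the primary time point, which is part of the outcome definition on which the sample size and the conclusion rest. The article is also not merely silent: it gives two time points the same status.

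Several stronger readings are tempting, and the article does not support them:

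- **That the false-positive rate is above 5% as planned.** A reader might infer this, but it follows only if either time point suffices. The article does not say so.
- **That the subscales multiply the primary tests.** The three subscales are mentioned only to describe the instrument. The hypothesis mentions emotion regulation beside resilience but ties it to no instrument. No section declares subscale tests as primary, so no error rate should be computed for them.
- **That the sample size cannot carry two tests.** At the stated d = 0.62, 64 per group gives 89% power even with a full Bonferroni split. Power would fall to 71%, with 78 per group needed, only at d = 0.50, which the article does not state.
- **That two separate models are planned.** The wording does not settle this. The calculation needs only one group comparison at each time point, whether from one model or two.

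It is also right that the two-sided figures include errors favouring the control group, which is why the one-directional rates are shown beside them.

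**Conclusion.** The point holds in a conditional form. The article sets two equal time points for the primary outcome, names none as primary and gives no success rule, while planning one two-sided test at 0.05. If either time point may count, the two-sided false-positive rate is about 7.0% to 9.1% for ρ from 0.9 to 0.5, with 9.75% under independence. These sizes rest on the assumed correlations, on the normal approximation and on the either-suffices rule. The missing reading of a split result rests on none of them. The inflation is moderate and the remedy nearly free, so the plan should be changed.

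**What to change.** Name one primary endpoint: the Psychological Resilience Scale total score at one stated time point, at two-sided α = 0.05. Which time point is the sponsor's choice, fixed before any outcome data are seen. Post-intervention is one example; the article gives no reason to prefer it to two months, and either controls the error equally well. Test the total score at the other time point in fixed sequence, also at 0.05, only if the first test is significant. State in the Sample size calculation section that the planned effect refers to the chosen time point.

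This takes a few sentences and needs no more participants. The cost is that an effect seen only at the second-ranked time point could be reported but not claimed as the primary result.

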## Discussion

This paper describes the study protocol of a randomized controlled trial of a resilience-enhancement program for mothers, focused on emotion regulation. In contrast to previous parenting programs, which focus on teaching appropriate parenting skills, the novelty of this trial lies in its utilization of a CBT-based resilience-enhancement program for mothers for the purpose of the prevention of child-maltreatment. Our conceptual hypothesis is that the resilience enhancement training given to mothers in the intervention group will improve their psychological resilience and emotion regulation through the application of CR compared to mothers in the discussion group.

We further predict that, with these newly acquired skills, the intervention group will improve its level of self-esteem, family functioning and coping strategies and that this will have a positive impact on the families and children of these mothers.

If this program proves to be effective in enhancing resilience and ER among mothers, it may offer a new way to prevent maltreatment of children and protect the mental health of children and families.

## Data Availability

Not applicable.

## Abbreviations

CBT: cognitive behavioral therapy
CR: cognitive reappraisal
ER: emotion regulation
